### Data management, monitoring and confidentiality

The study technical platform database BASS4, provided by Karolinska Core Facilities, will be used to gather and securely store data in encrypted form, behind two-factor authentication and accessible only to authorized research personnel. Self-report forms will primarily be completed online, meaning that the data is immediately stored in BASS4. Information collected through methods other than self-report forms (such as self-report forms for patients who wish to fill them in on paper) will be manually entered into BASS4 by research assistants, using predefined templates to ensure data integrity and adherence to expected value ranges. Several strategies will be used to enhance participant retention, including automated text reminders at each follow-up, phone calls from research assistants for incomplete forms, and the option to complete a shorter version including only key questionnaires or respond to the primary outcome measure (WHODAS-8) by phone.

Standardized coding practices will be employed for any necessary data encoding. Following data collection, all information will be pseudonymized and assigned unique identifiers, with access restricted to the principal investigator and university archivists. Other members of the project team will have access to pseudonymized data. Given the trial’s low anticipated risk to participants and the absence of mandatory data monitoring for psychological intervention trials in Sweden, the decision was made to forego a data monitoring committee due to financial reasons.

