#### Patient outcomes

Patient outcomes will be primarily assessed through self-report forms, complemented by a semi-structured interview to gather more detailed information about the patient experience. Self-report measures are completed at the pre-measure timepoint – prior to or shortly after the initial visit at the PCC – with follow-ups at 4 weeks (FU4), 8 weeks (FU8), and 12 weeks (FU12), with FU12 serving as the primary endpoint. A long-term follow-up is conducted one year later (FU52). The number of visits and contacts during this period is variable in both BI and GSH treatments. All timepoints are relative to the completion of the pre-measure. The interview, available in the Supplementary materials B, is conducted at the FU12 timepoint and allows patients to provide detailed feedback on their satisfaction, adverse events, treatment content, goals, and perceived changes in symptoms and quality of life.

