##### Patient experiences, satisfaction, adverse events and treatment credibility

Patient experiences and perceptions will be measured using self-report forms, as well as further explored qualitatively during the FU12 interview. Subjective change in the patient’s condition since seeking care will be assessed using the one-item Patient Global Impression - Improvement (PGI-I) scale [64]. Satisfaction with care will be measured using a combination of four items [2, 5, 7, 8] from the Client Satisfaction Questionnaire (CSQ) [65], the Session Rating Scale (SRS) [66], and nine additional items tailored for Primary Care Behavioral Health (PCBH) settings to gauge patients’ perceptions and attitudes towards their care providers (see Supplementary materials C). The 5-item Treatment Credibility Scale evaluates how credible and effective participants perceive their treatment to be, enabling analyses of any link between perceived effectiveness and actual outcomes [67]. To evaluate treatment side effects, patients will complete an Adverse Events questionnaire, offered in both a concise (3 items) version at the FU4 and FU8 timepoints, and a more comprehensive version (9 items) at FU12, both available in Supplementary materials C. These allow patients to report and describe any unwanted treatment effects or events they may have experienced. Any adverse events requiring immediate action will be promptly reported to the responsible PCC.

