#### Treatment content

Data on which interventions therapists use in each treatment modality will be extracted from medical records. Patients’ recollections of these interventions and which strategies they continue to use post-treatment will also be gathered qualitatively during the FU12 interview. Comparisons between treatment content in medical records, patient recollections and protocols (in GSH), as well as the broader evidence base (in BI), will be utilized to analyze variations in treatment outcomes. Medical records and interview responses will be coded using an inductive approach, where codes are developed directly from the data rather than from predefined categories. Double coding will be used to test inter-rater reliability, and any discrepancies will be resolved through discussion.

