#### Healthcare utilization and costs

The number of visits for each treatment type will be extracted from medical records. Treatment duration in hours will be calculated based on each site’s standard session length for in-person visits and phone or video consultations. Healthcare resource utilization and societal economic impact will be assessed using multiple measures. Direct treatment costs will be calculated based on the cost for self-help books, the number and duration of patient contacts, and the type of healthcare professional delivering the treatment. The Trimbos and iMTA questionnaire on Costs associated with Psychiatric Illness (TiC-P) will capture data on patient work productivity, including absenteeism due to sick leave, reduced efficiency while working, and productivity loss at home, as well as medication usage. The EQ-5D will be used to evaluate overall health-related quality of life for economic analyses.

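### All stated adverse-event sources depend on the patient responding, so harms may be under-ascertained in patients lost to follow-up, and the between-arm comparison is conditional on response

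*Protocol article*

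**What the plan says.** In the protocol article, the section on patient experiences, satisfaction, adverse events and treatment credibility sets the method: "To evaluate treatment side effects, patients will complete an Adverse Events questionnaire". Table 2 lists a 3-item form at FU4 and FU8 and a 9-item form at FU12, and none at FU52. Of these forms the section says: "These allow patients to report and describe any unwanted treatment effects or events they may have experienced". The Patient outcomes section adds an interview at FU12 that "allows patients to provide detailed feedback on their satisfaction, adverse events, treatment content, goals" and perceived change. For urgent events the stated direction is from the study to the clinic: "Any adverse events requiring immediate action will be promptly reported to the responsible PCC". No flow from the clinic back to the study is described.

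The section Data management, monitoring and confidentiality lists the retention measures: text reminders, phone calls about incomplete forms, and "the option to complete a shorter version including only key questionnaires or respond to the primary outcome measure (WHODAS-8) by phone". The contents of the shorter version are not listed.

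Medical records are already used elsewhere. Under Treatment content: "Data on which interventions therapists use in each treatment modality will be extracted from medical records". Under Healthcare utilization and costs: "The number of visits for each treatment type will be extracted from medical records". They also supply baseline diagnoses and medications and, with the CRF, the fidelity ratings. Finding harm events is not among the stated uses.

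Research question 4 (Aim and purpose) compares adverse events between care models and between treatments. The Data analysis plan confirms that this is done at both levels.

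**The concern.** A harm measure that works only when the patient answers is weakest for the events that matter most. A patient who has died, is incapacitated or has broken off all contact supplies no form and no interview. If worsening makes a patient less likely to answer, the observed event rate is too low. If response also differs between arms, the comparison is biased as well.

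The phone route adds a second gap. A patient who gives only the WHODAS-8 by phone counts as observed for the primary outcome but provides no adverse-event form in that contact. Completeness reported for the primary outcome may then overstate completeness for harms.

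At stake is how far a statement that the two care models do not differ in adverse events can be trusted. The trial has no data monitoring committee, so these data will carry most of the weight on safety.

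**Working it through.** **1. Sources side by side.**

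| Source | Stated use | Needs the patient to respond? |
|---|---|---|
| Adverse-event form, FU4 and FU8 (3 items) | Harms | Yes |
| Adverse-event form, FU12 (9 items) | Harms | Yes |
| Interview, FU12 | Harms, among other topics | Yes |
| Medical records | Diagnoses, medication, treatment content, fidelity, visits | No, but not used for harms |
| CRF | Fidelity, retrospective indication | No, but not used for harms |

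Every source in the harms rows depends on response. The two that do not are used for other purposes.

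**2. The plan's own figure.** Inputs from Power analysis: d = 0.20, alpha 0.05 (two-sided, inferred from the contrast with the one-sided non-inferiority test), 80% power, 20% missing at FU12.

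- Per arm: 2 × (1.960 + 0.842)² / 0.20² ≈ 393; total 786.
- With 20% missing: 786 / 0.80 = 982.5, rounded up to 983. The stated figure is reproduced and is not in dispute.
- Expected without the primary outcome at FU12: 0.20 × 983 = 196.6, about 197.

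**3. What the 197 does and does not mean.** It counts patients without the primary outcome at FU12. It does not count patients with no adverse-event data at all, because forms are also given at FU4 and FU8 and there is an interview. The article gives no rate for patients missing at every wave. For the FU12 form alone, 197 is a floor under the planning assumption if those patients return no other FU12 form. Each patient who gives only the WHODAS-8 by phone adds one. If 0, 5, 10 or 20 percentage points of the sample were such patients (assumed), 197, 246, 295 or 393 would lack an FU12 form.

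**4. How much one wave could hide (all rates assumed).** Suppose 10% of FU12 responders report an event and 20% do not respond.

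- No non-responder had an event: 0.80 × 0.10 = 8%.
- Every non-responder had one: 0.08 + 0.20 = 28%.

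These are worst-case limits for the FU12 form only, not for the whole trial. As a less extreme case, let non-responders have three times the risk of responders. The unseen share of events is 3m / (1 − m + 3m), where m is the share not responding. At m = 0.20 this is 0.60 / 1.40 = 43%. At m = 0.30 it is 0.90 / 1.60 = 56%. With equal risk it is simply m.

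**5. How a difference between arms could disappear (all inputs assumed).** Take non-response of 25% and 15%, and event rates of 10% in responders and 30% in non-responders.

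- Arm A: 0.75 × 0.10 + 0.25 × 0.30 = 15.0%.
- Arm B: 0.85 × 0.10 + 0.15 × 0.30 = 13.0%.
- Observed: 10% in each arm.

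This shows the mechanism. Nothing in the article says that response will differ in this way.

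**The case against.** The strongest reply is that the article offers several ways to reach patients. Research assistants phone about incomplete forms, and the shorter version may well include the 3-item adverse-event form. Follow-up is timed from the pre-measure, not from attendance, so a patient who leaves treatment is still contacted. Someone admitted in week 5 can report it at FU12. Both arms have the same forms, schedule and reminders, and participants are blind to the treatment options. This is also a condensed article that mentions SOPs and CRFs, so a fuller procedure for serious events may exist elsewhere. These points stand, and they rule out several stronger readings.

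- A reader might infer that serious events and disengaged patients are simply missed. The documents support only possible under-ascertainment, chiefly in death, incapacity and full loss to follow-up.
- A reader might infer that 197 patients give no adverse-event data, or that missing harm data must exceed 20%. Neither follows: earlier waves and the interview may cover some of them, and the number of phone-only responders is not given.
- A reader might infer that adverse events will be imputed from responders. The Data analysis plan describes multiple imputation in general and does not mention adverse events.
- A reader might infer that the monitoring committee was dropped on the low-risk premise alone. The article also cites the absence of a requirement for such trials in Sweden, and cost.
- Differential response between arms is plausible but not shown.

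The reply does not remove the main point. The article says how harms are evaluated, and each method it names depends on the patient answering. That is a stated choice of data source, and it holds if the plan is followed exactly.

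**Conclusion.** The point holds as a limit on ascertainment. It is not an error or a contradiction in the plan. All stated harm sources are patient-reported, and the phone route names only the WHODAS-8. The adverse-event comparison in research question 4 is therefore conditional on response, and completeness of the FU12 adverse-event form can be lower than that of the primary outcome.

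The size cannot be fixed from the document. About 197 of 983 patients is the planned shortfall in the primary outcome at one wave; the shortfall in harm data over all waves may be smaller or larger. The limits and scenarios in the working rest on assumed event rates, risk ratios and response rates. The conclusion also assumes that no document outside the article specifies a harm source that does not depend on response. It is a cheap improvement to a secondary comparison and leaves the primary analysis untouched.

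**What to change.** 1. In the medical-record extraction already planned, add a short fixed list of harm events, for example death, self-harm, emergency or inpatient psychiatric care, and referral because of worsening. Extract it for every included patient in both arms over the same window. Include patients later judged to need specialised or medical care, whom the Data analysis plan removes from most analyses.
2. Report record-based and self-reported harms separately, by randomised arm, with the adverse-event response rate per arm and wave.
3. State what the shorter version contains. For any follow-ups still to come, the existing 3-item form may be added to phone contacts, and this mid-trial change should be disclosed. Its benefit is small: the protocol was written toward the end of data collection, and recruitment was expected to end in May 2025.

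The cost is a few extra fields in an extraction that takes place anyway, and slightly longer calls for the remaining patients. Reporting response rates needs no new data. Primary care records may miss events recorded elsewhere, so the record-based counts should be presented as a lower bound.

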### Power analysis

The power analysis is based on the primary outcome and endpoint, specifically the sum of eight items from WHODAS-12 at FU12. In the pilot trial (manuscript in preparation), a preliminary effect of 0.18 (Cohen’s *d*) was observed between the two care models after eight weeks of treatment. However, at that time, some of the GSH interventions were still ongoing. Many self-help books in the study are structured into 10–12 chapters, completed at a pace of one per week, and many of the studies on the internet-based interventions have a duration of 10–12 weeks [32, 34, 35, 37, 44]. Given this, the endpoint of this full-scale RCT was adjusted to twelve weeks, under the assumption that patients would have finished their treatments, which may produce a somewhat larger effect. A previous trial using similar GSH interventions reported slightly stronger effects [24]. Considering these factors, we estimate an expected between-group effect size of *d* = 0.20. To achieve 80% power with an alpha of 0.05 while accounting for 20% missing data at FU12, a total sample size of 983 patients is required [70]. Recruitment will continue until the power target is reached, with efforts to identify and include new PCCs as necessary. The pilot study (manuscript in preparation) demonstrated an acceptable inclusion rate.

If the primary analysis fails to establish superiority, a secondary analysis will assess whether the core PCBH model is non-inferior to the extended model (PCBH + GSH). No established non-inferiority margin exists for WHODAS-12 in mental health patients in primary care, and even less so for the 8-item version used in this study. Therefore, although not ideal, we reference a previously established non-clinically relevant difference of *d* = 0.24 from a meta-analysis of patients receiving psychological treatment for depression [71]. However, as this threshold is based on disorder-specific measures and treatments, we anticipate that the transdiagnostic WHODAS will be less sensitive to change and will therefore set the non-inferiority margin to *d* = 0.20. To achieve 80% power with an alpha of 0.05, assuming 20% missing data, 775 patients will be required [70]. This falls within the target sample size for the primary analysis. The smaller sample size required for the non-inferiority analysis, despite the identical effect size used, is due to the use of a one-sided test.

For the secondary analyses of the subgroups of patients deemed suitable for structured treatment (CORE-I-BI vs. EXT-I-GSH), the between-group effect is expected to be larger, but the number of patients will also be lower. Given these uncertainties, a separate power analyses for this secondary research question is not performed.

### Data analysis plan

Due to the pragmatic nature of the study, where randomization occurs early – after patients have been identified and invited to participate, but before they are formally included in the trial – there is an increased risk of randomized participants during assessment or treatment being deemed unsuitable for both GSH and BI due to a need for specialized or primarily medical treatment. These participants will be excluded from most analyses but are expected to be randomly distributed between study arms. Another consequence of the pragmatic design is that patients may complete the pre-treatment measures up to a week after their initial visit to manage the usually very brief waiting time in PCBH. This could particularly impact within-group BI effects, as treatment begins during the first visit. To address this, a sensitivity analysis excluding late responses will be conducted, along with an analysis of missing data to evaluate its potential impact.

Several comparisons will be made to address the research questions. For research questions (1) and (3), we will conduct between-group comparisons on primary and secondary measures at the care model level, specifically comparing all participants in PCBH group with those in the PCBH + GSH group. To address research question (2), we will compare the subgroup of patients who received GSH (the EXT-I-GSH group) within the PCBH + GSH model with those who were retrospectively assessed as indicated for structured treatment but were randomized to the core PCBH arm and therefore did not receive GSH (the CORE-I-BI group). For the subgroup analysis examining whether GSH has a greater impact on conditions where the protocol is expected to have more specific effects (insomnia, panic disorder, social phobia, health anxiety disorder, and OCD) compared to conditions the effects are expected to be more general and non-specific (depression, GAD, and stress), analyses will evaluate whether patients in the former group show larger differences between GSH and BI than patients in the latter group. Research question (4) will be analyzed at both the care model and treatment type levels, as factors such as patient satisfaction, treatment content, patient behavior, and adverse events may be influenced by both the assessment and treatment strategies.

For research questions (5) and (6), the analysis groups will be defined based on treatment rather than the model of care. It is therefore essential to clarify how comparison groups are categorized, as they do not align fully with the randomized groups. There is only one subgroup of patients that receive GSH – the patients in the PCBH + GSH arm assessed by the clinician as suitable for GSH (the EXT-I-GSH group). In contrast, patients receiving BI can be divided in several groups, all presented in Table 3. Analyses will be conducted on various combinations of patients receiving BI to account for potential differences among these groups. For example, CORE-N-BI and EXT-N-BI may present with more complex symptoms or social challenges compared to CORE-I-BI – or alternatively, they may have less complex, transient life stressors. Additionally, the diagnostic assessment in the PCBH + GSH model may influence the effectiveness of BI in either direction, necessitating comparisons between patients who received BI in the core model and those in the extended model.

**Table 3 Tab3:** Treatment-level analysis groups

	Core PCBH arm		PCBH + GSH arm	
	CORE-I-BI	CORE-N-BI	EXT-I-GSH	EXT–N-BI
**All patients receiving GSH**			X	
**All patients receiving BI**	X	X		X
**Receiving BI despite an indication for structured treatment**	X			
**Receiving BI in accordance with the indicated treatment**		X		X
**Receiving BI following an extended assessment confirming BI as appropriate**				X
**Receiving BI after the contextual interview**	X	X		

Notes. CORE-I-BI = Patients receiving brief interventions (BI) within the core PCBH model who were retrospectively assessed as suitable for structured treatment

CORE-N-BI = Patients receiving brief interventions (BI) within the core PCBH model who were retrospectively assessed as not suitable for structured treatment

EXT-I-GSH = Patients receiving guided self-help (GSH) after undergoing an extended diagnostic assessment within the PCBH + GSH model, where they were deemed suitable for structured treatment

EXT-N-BI = Patients receiving brief interventions (BI) after an extended diagnostic assessment within the PCBH + GSH model, where they were not deemed suitable for structured treatment

In question (5), the difference in variation of treatment outcomes due to intervention (primarily comparing EXT-I-GSH with CORE-I-BI) will be evaluated by testing if the variation in FU12-scores differs between the two groups using an F-test. To put the difference in variation after treatment in context, the same type of F-test will be made on PRE-scores. The first question in (6) focuses solely on BI and how the therapists’ choice of methods affects outcome. This question requires rating all identified therapeutic methods based on the extent to which they are deemed to have an empirically supported effect for the condition they address. The protocol for these ratings will be developed once all therapeutic methods are identified and prior to exploring their relation to outcomes. The main analysis will be made on all patients receiving BI, regardless of subgroup. The second question in (6) examines potential differences between the subgroups receiving BI. For the third question in (6), only patients receiving GSH will be included, and ratings of therapist adherence will be used to explore its overall relationship to outcomes, as well as for subgroups of patients where GSH manuals with expected specific versus non-specific effects are used. For the final question in (6), relationships between treatment content and outcomes will be explored for all patients, regardless of care model or subgroup.

For research questions (7), (8), and (9), the focus shifts to exploring the feasibility and fidelity of implementing the PCBH + GSH model at scale across multiple PCBH PCCs. To address research question (7), we will examine the proportion of patients who are deemed suitable for GSH following the extended diagnostic assessment. A hierarchical model using a binomial distribution will be used to evaluate whether the suitability rate varies significantly between as well as within centers over time, and to explore any factors contributing to these variations. In research question (8), we will use Hierarchical Linear Models to investigate how patient-related outcomes are affected by interventions and vary across centers and therapists, as well as the factors contributing to these differences. This will help identify potential barriers and facilitators for the successful implementation of both the core and extended PCBH models across different settings. Finally, research question (9) will explore the fidelity of both GSH and BI treatments. Specifically, we will examine how closely clinicians adhere to GSH principles within the PCBH framework, particularly in areas where GSH and PCBH principles may conflict, as well as generally assess the quality of the BI interventions. Fidelity scores will be analyzed descriptively to determine the frequency of low, good-enough and good fidelity ratings. A *t*-test will be used to evaluate whether the mean fidelity score is 3 (good-enough) or higher. Additionally, fidelity will be analyzed across clinicians and PCCs using chi-square tests and logistic regression to identify variability and the factors contributing to it. This will help assess the overall quality of treatment delivery and identify areas that may need further support or adjustment for large-scale implementation.

The primary statistical methods employed will be Hierarchical Linear Models and Generalized Estimating Equations. Missing data will be handled using multiple imputation techniques that align with the missing data mechanism, while accounting for the multilevel structure of the data. Imputation models will be specified to reflect the underlying data structure, provided the complexity does not hinder model convergence. The analyses will consider the hierarchical structure of the data, such as nesting patients under therapists under PCCs for patient outcomes. The variance of each grouping level in the models will be calculated as the intra-class correlation (ICC) metric. An ICC > 0.10 will be used as a cutoff for the relevance of including it in the final model.

The non-inferiority analysis will be conducted by estimating the mean differences and standard errors at FU12, using Rubin’s rule after performing multiple imputations for missing data. A one-sided 95% CI (corresponding to a 90% two-sided CI) will be calculated for the estimated mean difference. To determine the outcome, we will compare the lower bound of the confidence interval with the non-inferiority margin of *d* = 0.20. If the lower bound of the CI is above this margin, non-inferiority will be established, in line with prior recommendations [72]. For research question (4), which hypothesizes that GSH protocols with assumed specific effects may demonstrate superior outcomes compared to BI, we will include a dummy variable in the model to represent the type of GSH protocol used (specific or non-specific).

For Health Economic Analyses in question (3), effectiveness will be assessed by constructing quality-adjusted life-years (QALYs) based on EQ-5D. Incremental cost-effectiveness ratios (ICERs) will be calculated, and Monte Carlo simulation with non-parametric bootstrapping will be conducted to address the uncertainty of the ICER point estimates. Cost-effectiveness acceptability curves (CEACs) will be employed to examine cost-effectiveness across varying willingness-to-pay scenarios.

